#### Sample size justification and power calculations

In light of the project’s emphasis on the development of pragmatic measurement strategies that predict changes in the target problems, we powered the study to test for predictive validity. Calculations of a design effect (measure of how the design effects the standard error of the parameters) [81, 82] accounted for clustering. We computed ICC with repeated observations of clients at the clinic (*r*_*pb*_ = .01), clinician (*r*_*pb*_ = .01), and client (*r*_*pb*_ = .10) level in our prior research, assuming three clients per clinician, and six clinicians per cluster, and six observations per client, yielding a design effect of up to 2.04. We based the estimated number of observations per client to conservatively account for potential 37% client-level attrition and missing data during the treatment. For the growth curve analyses to assess whether the quality measure predicts symptom change (our primary analysis), the probability of a type 1 error (alpha) at two-tailed .05 power exceeds .80 for an effect size of *r* = .30, which corresponds with small-to-medium effects of fidelity on symptoms in prior CBT fidelity research [68, 83]. We also projected a sample size to be sufficient to conduct separate analyses and test for interactions with disorder (PTSD vs. depression vs. anxiety), app vs. paper form, and other variables of interest, and detect an effect size of .50, a medium effect.

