#### Clinical outcome predictions

We expect that clients whose sessions receive higher quality ratings will exhibit larger decreases in symptoms compared to clients whose sessions had lower ratings. Based on previous research suggesting that it is important to assess fidelity in early sessions to avoid temporal confounds between process variables and outcomes [22, 68, 74, 75], we expect that quality in earlier sessions will more accurately reflect the contributions of session quality and clinician skill (rather than client factors) than that in later sessions. Primary analyses will focus on quality in sessions 1–6. We will cross-validate prediction models as a way of checking internal validity (generalization error).

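### The printed ICCs and cluster sizes give a design effect of 2.52 or 2.74, above the stated ceiling of 2.04; the main power claim survives, but its basis needs restating

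*Protocol article*

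**What the plan says.** All the inputs stand in the protocol article under *Sample size justification and power calculations*. The correlations come from the team's earlier research: "ICC with repeated observations of clients at the clinic (*r*_*pb*_ = .01), clinician (*r*_*pb*_ = .01), and client (*r*_*pb*_ = .10) level". The cluster structure follows, "assuming three clients per clinician, and six clinicians per cluster, and six observations per client", and then the result, "yielding a design effect of up to 2.04". No formula is shown; two references are cited for the method.

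The observation count is explained this way: "We based the estimated number of observations per client to conservatively account for potential 37% client-level attrition and missing data during the treatment". The section then claims power above .80, two-sided alpha .05, for r = .30 in the growth-curve analysis of whether quality predicts symptom change. For separate analyses by disorder and for interactions, it says the sample can "detect an effect size of .50, a medium effect", without naming the metric.

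Three other sections bear on this. *Client inclusion criteria* gives 360 clients. *Recruitment and informed consent* plans a primary symptom measure at every session, for up to 16 sessions. *Clinical outcome predictions* says: "Primary analyses will focus on quality in sessions 1–6".

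**The concern.** A design effect converts a count of correlated observations into an effective sample size. The words *up to* present 2.04 as a ceiling, so a reader takes it as the worst case for clustering. If the printed inputs give a larger value, clustering is understated and the precision behind the power statement is overstated. The primary aim is predictive validity, and the study is said to be powered for it, so the figure should be reproducible from the inputs beside it.

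Two ambiguities in the same paragraph add to this. Six observations could mean symptom measures or quality scores, and the 37% allowance fits only the first. The .50 effect size has no metric.

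**Working it through.** **Inputs.** Observations per client m = 6; clients per clinician c = 3; clinicians per cluster k = 6. That makes 18 observations per clinician and 108 per cluster. ICCs: client .10, clinician .01, clinic .01. Clients: 360. Total observations: 360 × 6 = 2,160.

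**Attempt to reproduce 2.04.** None of these readings gives it:
- Client level only: 1 + 5(.10) = 1.50
- Clinician level only: 1 + 17(.01) = 1.17
- Clinic level only: 1 + 107(.01) = 2.07, which ignores the largest ICC
- Product of client and two clinician-size factors: 1.50 × 1.17 × 1.17 = 2.05, not a standard form
- Client and clinician only: 1 + 5(.10) + 12(.01) = 1.62, or 1 + 5(.11) + 12(.01) = 1.67

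**Standard nested design effect.** An observation shares its client with m − 1 = 5 others, its clinician but not its client with m(c − 1) = 12, and its clinic but not its clinician with mc(k − 1) = 90.
- ICCs as variance shares (correlations .12, .02 and .01): 1 + 5(.12) + 12(.02) + 90(.01) = 1 + .60 + .24 + .90 = **2.74**
- ICCs as pairwise correlations (.10, .01 and .01): 1 + 5(.10) + 12(.01) + 90(.01) = 1 + .50 + .12 + .90 = **2.52**

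The stated figure is 2.04/2.74 = .74 or 2.04/2.52 = .81 of these, so 26% or 19% too low.

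**Rounding.** Each ICC is printed to two decimals, so each may be off by .005.
- Pairwise form: from 1 + 5(.095) + 12(.005) + 90(.005) = 1.99 to 1 + 5(.105) + 12(.015) + 90(.015) = 3.06
- Variance-share form: from 1 + 5(.105) + 12(.010) + 90(.005) = 2.10 to 1 + 5(.135) + 12(.030) + 90(.015) = 3.39

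Rounding reaches 2.04 only at the low edge of the pairwise form.

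**Consequence, observation as the unit.** Effective N = 2,160/DE. Detectable r at 80% power = tanh[(1.96 + 0.84)/√(N − 3)]. Power at r = .30 = Φ[atanh(.30)·√(N − 3) − 1.96].

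| Design effect | Effective N | Detectable r | Power at r = .30 |
|---|---|---|---|
| 2.04 | 1,059 | .086 | > .99 |
| 2.52 | 857 | .096 | > .99 |
| 2.74 | 788 | .100 | > .99 |

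**Harsher check, 360 clients divided by the same design effect.** Power at r = .30 is .983 at 2.04, .955 at 2.52 and .939 at 2.74. An effective N of 85 is enough for 80% power, so 85 × 2.74 = 233 units would suffice.

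**Observation count.** Against 16 planned symptom measures, 37% loss leaves 16 × .63 = 10.1, so six is already a reduced number. Against the sessions 1–6 quality scores, six is complete data, and 37% loss would leave 6 × .63 = 3.8. On that second reading the design effect also falls, to 1.92 (pairwise) or 2.05 (variance shares). Effective N is then 1,361/1.92 = 709 or 1,361/2.05 = 663, and power at r = .30 stays above .99.

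**Metric of .50.** r = .30 converts to d = 2(.30)/√(1 − .09) = .63, and d = .50 corresponds to r = .24. Whether .50 is larger or smaller than the main target effect depends on the missing label.

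**The case against.** The best defence of 2.04 is that the formula sits behind cited references, an article may condense, and the ICCs are rounded. Unrounded values could yield 2.04, and 2.05 and 2.07 come from other readings. This stands in part: the figure cannot be called impossible. But it needs ICCs near the bottom of their rounding ranges together with the pairwise definition. The near misses either drop the client ICC or are non-standard, and both are above a figure offered as an upper bound. The variance-share form at 3.8 observations also gives 2.05, but the paragraph states six.

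Four stronger readings may tempt a reader, and the document does not support them.

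- *Power falls below .80.* Removing 37% of clients (227 left) and dividing by 2.74 gives .79. That applies an observation-level design effect to clients. It also keeps three clients per clinician after the loss, and may deduct attrition twice, since the plan puts it in the observation count. With 1.89 clients per clinician the design effect is 2.27 and power is .86. With the within-client term removed (2.74/1.60 = 1.71), power is .94.
- *Six observations leave no room for attrition.* The power statement concerns growth curves of symptoms, measured at up to 16 sessions. The sessions 1–6 window is set for the quality predictor and does not cap the outcome measures.
- *The origin of the slip is known.* 17 × .12 equals 2.04, but so does 1.50 × 1.36. With no formula shown, any origin is a guess.
- *The effect sizes contradict each other.* The .50 concerns different tests from r = .30, and using different metrics for a continuous predictor and a group contrast is ordinary. The clinical-meaning threshold under *Analyses* gives no number to conflict with. Only the label is missing.

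**Conclusion.** The stated ceiling of 2.04 does not follow from the inputs printed with it. The standard result is 2.74 or 2.52, depending on how the ICCs are defined. The effective number of observations is overstated: 1,059 against 788 to 857. The detectable correlation is about .096 to .100, not .086.

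The conclusion drawn from it holds. Power at r = .30 is above .99 with observations as the unit, and .94 to .96 when the 360 clients are divided by the corrected design effect. This is an error in a supporting figure, with no consequence for enrolment or for the main power conclusion.

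The assumptions are equal cluster sizes, the usual nested formula, the printed ICCs taken at face value, and the Fisher z approximation. The unit of the power calculation is not stated, so both are shown. The observation count and the .50 label are points to clarify; neither is shown to be wrong.

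**What to change.** In *Sample size justification and power calculations*:

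1. Restate the design effect as 2.74 (variance shares) or 2.52 (pairwise correlations), with the formula and the ICC definition. If 2.04 came from unrounded ICCs, print those and the formula instead.
2. Name the unit of the power calculation, observation or client, and give the effective sample size and minimum detectable effect in that unit.
3. Say whether the six observations per client are symptom measures or sessions 1–6 quality scores. If they are quality scores, give the count expected after the 37% loss.
4. Name the metric of the .50 effect size.

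The cost is a few rewritten sentences in one paragraph and slightly less favourable supporting figures. Enrolment, data collection and the analysis model stay as they are.

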## Discussion

To date, there is no feasible and easily adoptable way to effectively assess clinician fidelity of CBTs. This study aims to refine and test a unique method of leveraging data generated through routine clinical procedures to assess quality to (1) develop a scalable general CBT quality measure based on work samples rather than self-report or observation and (2) to evaluate the reliability, validity, and feasibility of different strategies for collecting these materials. Our method poses little additional burden to clients or clinicians. Because it uses routine clinical materials, it allows for a less “invasive” review of a random selection of sessions by a quality monitor or supervisor. Since treatments are sometimes modified in practice settings [8], it will be designed to apply to modifications to worksheets that are adapted to meet client needs. To our knowledge, this will be the first instrument of this nature to be developed and validated. It will thus fill a critical gap in the field and has the potential to make large-scale quality monitoring in research and practice settings more feasible and efficient. Scalable methods of quality monitoring are vital to efforts to study and promote the implementation of EBPTs [84, 85]. This study has strong potential to impact fidelity monitoring strategies for a variety of CBTs due to shared elements across CBTs [36]. A less burdensome method can dramatically increase feasibility of ongoing quality monitoring. Validation across platforms (mobile app and traditional paper forms) and data on the feasibility and acceptability of each of these platforms is an additional innovation that will yield actionable data to inform implementation. This in turn can promote continued consumer access to high-quality delivery of CBT and other EBPTs [9, 16, 22], and protect the significant investment in implementation across multiple systems.

## Abbreviations

app: Application
BAI: Beck’s anxiety inventory
CBT: Cognitive behavioral therapy
CPT: Cognitive processing therapy
CTRS: Cognitive therapy rating scale
EBPT: Evidence-based psychosocial treatment
HIPAA: Health Insurance Portability and Accountability Act
ICC: Intraclass correlations
IRB: Institutional review board
PCL-5: Posttraumatic stress disorder checklist-5
PHQ-9: Patient health questionnaire-9
PTSD: Posttraumatic stress disorder
SD: Standard deviation
VA: Veterans affairs
